### 1.3 Potential Risks and Benefits of Treatment Options

### 1.3.1 Potential risks of IBI362 based on preclinical safety studies

[REDACTED]

[REDACTED]

### 1.3.2 Potential risks of IBI362 based on clinical safety studies

[REDACTED]

[illegible]

| Bar Index | Relative Length (approximate) |
|-----------|-------------------------------|
| 1         | 100%                          |
| 2         | 85%                           |
| 3         | 65%                           |
| 4         | 95%                           |
| 5         | 100%                          |
| 6         | 98%                           |
| 7         | 99%                           |
| 8         | 99%                           |
| 9         | 95%                           |
| 10        | 90%                           |

[REDACTED]

[REDACTED]

[REDACTED]

[REDACTED]

[REDACTED]

[REDACTED]

[REDACTED]

[REDACTED]

|                          |                          |                          |                          |                          |                          |                          |
|--------------------------|--------------------------|--------------------------|--------------------------|--------------------------|--------------------------|--------------------------|
| [REDACTED]
[REDACTED] | [REDACTED]               |                          |                          |                          |                          | [REDACTED]
[REDACTED] |
|                          | [REDACTED]
[REDACTED] | [REDACTED]
[REDACTED] | [REDACTED]
[REDACTED] | [REDACTED]
[REDACTED] | [REDACTED]
[REDACTED] |                          |
|                          | [REDACTED]               | [REDACTED]               | [REDACTED]               | [REDACTED]               | [REDACTED]               |                          |
| [REDACTED]               |                          |                          |                          |                          |                          |                          |
| [REDACTED]               | [REDACTED]
[REDACTED] | [REDACTED]               | [REDACTED]               | [REDACTED]               | [REDACTED]
[REDACTED] | [REDACTED]
[REDACTED] |
| [REDACTED]               |                          |                          |                          |                          |                          |                          |
| [REDACTED]               | [REDACTED]               | [REDACTED]               | [REDACTED]               | [REDACTED]               | [REDACTED]               | [REDACTED]
[REDACTED] |
| [REDACTED]               | [REDACTED]
[REDACTED] | [REDACTED]
[REDACTED] | [REDACTED]               | [REDACTED]               | [REDACTED]               | [REDACTED]
[REDACTED] |
| [REDACTED]               | [REDACTED]               | [REDACTED]               | [REDACTED]               | [REDACTED]               | [REDACTED]
[REDACTED] | [REDACTED]               |
| [REDACTED]               | [REDACTED]               | [REDACTED]               | [REDACTED]               | [REDACTED]               | [REDACTED]               | [REDACTED]               |
| [REDACTED]               | [REDACTED]               | [REDACTED]               | [REDACTED]               | [REDACTED]               | [REDACTED]               | [REDACTED]               |
| [REDACTED]               | [REDACTED]               | [REDACTED]               | [REDACTED]               | [REDACTED]               | [REDACTED]
[REDACTED] | [REDACTED]               |
| [REDACTED]               | [REDACTED]               | [REDACTED]               | [REDACTED]               | [REDACTED]               | [REDACTED]               | [REDACTED]               |
| [REDACTED]               | [REDACTED]               | [REDACTED]               | [REDACTED]               | [REDACTED]               | [REDACTED]
[REDACTED] | [REDACTED]               |
| [REDACTED]               | [REDACTED]               | [REDACTED]               | [REDACTED]               | [REDACTED]               | [REDACTED]               | [REDACTED]               |
| [REDACTED]               | [REDACTED]               | [REDACTED]               | [REDACTED]               | [REDACTED]               | [REDACTED]               | [REDACTED]               |
| [REDACTED]               | [REDACTED]               | [REDACTED]               | [REDACTED]               | [REDACTED]               | [REDACTED]               | [REDACTED]               |
| [REDACTED]               | [REDACTED]               | [REDACTED]               | [REDACTED]               | [REDACTED]               | [REDACTED]               | [REDACTED]               |
| [REDACTED]               | [REDACTED]               | [REDACTED]               | [REDACTED]               | [REDACTED]               | [REDACTED]               | [REDACTED]               |
| [REDACTED]               | [REDACTED]               | [REDACTED]               | [REDACTED]               | [REDACTED]               | [REDACTED]               | [REDACTED]               |
| [REDACTED]               | [REDACTED]               | [REDACTED]               | [REDACTED]               | [REDACTED]               | [REDACTED]               | [REDACTED]               |
| [REDACTED]               | [REDACTED]               | [REDACTED]               | [REDACTED]               | [REDACTED]               | [REDACTED]               | [REDACTED]               |
| [REDACTED]               | [REDACTED]               | [REDACTED]               | [REDACTED]               | [REDACTED]               | [REDACTED]               | [REDACTED]               |
| [REDACTED]               | [REDACTED]               | [REDACTED]               | [REDACTED]               | [REDACTED]               | [REDACTED]               | [REDACTED]               |
| [REDACTED]               | [REDACTED]               | [REDACTED]               | [REDACTED]               | [REDACTED]               | [REDACTED]               | [REDACTED]               |
| [REDACTED]               | [REDACTED]               | [REDACTED]               | [REDACTED]               | [REDACTED]               | [REDACTED]               | [REDACTED]               |
| [REDACTED]               | [REDACTED]               | [REDACTED]               | [REDACTED]               | [REDACTED]               | [REDACTED]               | [REDACTED]               |
| [REDACTED]               | [REDACTED]               | [REDACTED]               | [REDACTED]               | [REDACTED]               | [REDACTED]               | [REDACTED]               |
| [REDACTED]               | [REDACTED]               | [REDACTED]               | [REDACTED]               | [REDACTED]               | [REDACTED]               | [REDACTED]               |
| [REDACTED]               | [REDACTED]               | [REDACTED]               | [REDACTED]               | [REDACTED]               | [REDACTED]               | [REDACTED]               |
| [REDACTED]               | [REDACTED]               | [REDACTED]               | [REDACTED]               | [REDACTED]               | [REDACTED]               | [REDACTED]               |
| [REDACTED]               | [REDACTED]               | [REDACTED]               | [REDACTED]               | [REDACTED]               | [REDACTED]               | [REDACTED]               |
| [REDACTED]               | [REDACTED]               | [REDACTED]               | [REDACTED]               | [REDACTED]               | [REDACTED]               | [REDACTED]               |
| [REDACTED]               | [REDACTED]               | [REDACTED]               | [REDACTED]               | [REDACTED]               | [REDACTED]               | [REDACTED]               |
| [REDACTED]               | [REDACTED]               | [REDACTED]               | [REDACTED]               | [REDACTED]               | [REDACTED]               | [REDACTED]               |
| [REDACTED]               | [REDACTED]               | [REDACTED]               | [REDACTED]               | [REDACTED]               | [REDACTED]               | [REDACTED]               |
| [REDACTED]               | [REDACTED]               | [REDACTED]               | [REDACTED]               | [REDACTED]               | [REDACTED]               | [REDACTED]               |
| [REDACTED]               | [REDACTED]               | [REDACTED]               | [REDACTED]               | [REDACTED]               | [REDACTED]               | [REDACTED]               |
| [REDACTED]               | [REDACTED]               | [REDACTED]               | [REDACTED]               | [REDACTED]               | [REDACTED]               | [REDACTED]               |
| [REDACTED]               | [REDACTED]               | [REDACTED]               | [REDACTED]               | [REDACTED]               | [REDACTED]               | [REDACTED]               |
| [REDACTED]               | [REDACTED]               | [REDACTED]               | [REDACTED]               | [REDACTED]               | [REDACTED]               | [REDACTED]               |
| [REDACTED]               | [REDACTED]               | [REDACTED]               | [REDACTED]               | [REDACTED]               | [REDACTED]               | [REDACTED]               |
| [REDACTED]               | [REDACTED]               | [REDACTED]               | [REDACTED]               | [REDACTED]               | [REDACTED]               | [REDACTED]               |
| [REDACTED]               | [REDACTED]               | [REDACTED]               | [REDACTED]               | [REDACTED]               | [REDACTED]               | [REDACTED]               |
| [REDACTED]               | [REDACTED]               | [REDACTED]               | [REDACTED]               | [REDACTED]               | [REDACTED]               | [REDACTED]               |
| [REDACTED]               | [REDACTED]               | [REDACTED]               | [REDACTED]               | [REDACTED]               | [REDACTED]               | [REDACTED]               |
| [REDACTED]               | [REDACTED]               | [REDACTED]               | [REDACTED]               | [REDACTED]               | [REDACTED]               | [REDACTED]               |
| [REDACTED]               | [REDACTED]               | [REDACTED]               | [REDACTED]               | [REDACTED]               | [REDACTED]               | [REDACTED]               |
| [REDACTED]               | [REDACTED]               | [REDACTED]               | [REDACTED]               | [REDACTED]               | [REDACTED]               | [REDACTED]               |
| [REDACTED]               | [REDACTED]               | [REDACTED]               | [REDACTED]               | [REDACTED]               | [REDACTED]               | [REDACTED]               |
| [REDACTED]               | [REDACTED]               | [REDACTED]               | [REDACTED]               | [REDACTED]               | [REDACTED]               | [REDACTED]               |
| [REDACTED]               | [REDACTED]               | [REDACTED]               | [REDACTED]               | [REDACTED]               | [REDACTED]               | [REDACTED]               |
| [REDACTED]               | [REDACTED]               | [REDACTED]               | [REDACTED]               | [REDACTED]               | [REDACTED]               | [REDACTED]               |
| [REDACTED]               | [REDACTED]               | [REDACTED]               | [REDACTED]               | [REDACTED]               | [REDACTED]               | [REDACTED]               |
| [REDACTED]               | [REDACTED]               | [REDACTED]               | [REDACTED]               | [REDACTED]               | [REDACTED]               | [REDACTED]               |
| [REDACTED]               | [REDACTED]               | [REDACTED]               | [REDACTED]               | [REDACTED]               | [REDACTED]               | [REDACTED]               |
| [REDACTED]               | [REDACTED]               | [REDACTED]               | [REDACTED]               | [REDACTED]               | [REDACTED]               | [REDACTED]               |
| [REDACTED]               | [REDACTED]               | [REDACTED]               | [REDACTED]               | [REDACTED]               | [REDACTED]               | [REDACTED]               |
| [REDACTED]               | [REDACTED]               | [REDACTED]               | [REDACTED]               | [REDACTED]               | [REDACTED]               | [REDACTED]               |
| [REDACTED]               | [REDACTED]               | [REDACTED]               | [REDACTED]               | [REDACTED]               | [REDACTED]               | [REDACTED]               |
| [REDACTED]               | [REDACTED]               | [REDACTED]               | [REDACTED]               | [REDACTED]               | [REDACTED]               | [REDACTED]               |
| [REDACTED]               | [REDACTED]               | [REDACTED]               | [REDACTED]               | [REDACTED]               | [REDACTED]               | [REDACTED]               |
| [REDACTED]               | [REDACTED]               | [REDACTED]               | [REDACTED]               | [REDACTED]               | [REDACTED]               | [REDACTED]               |
| [REDACTED]               | [REDACTED]               | [REDACTED]               | [REDACTED]               | [REDACTED]               | [REDACTED]               | [REDACTED]               |
| [REDACTED]               | [REDACTED]               | [REDACTED]               | [REDACTED]               | [REDACTED]               | [REDACTED]               | [REDACTED]               |
| [REDACTED]               | [REDACTED]               | [REDACTED]               | [REDACTED]               | [REDACTED]               | [REDACTED]               | [REDACTED]               |
| [REDACTED]               | [REDACTED]               | [REDACTED]               | [REDACTED]               | [REDACTED]               | [REDACTED]               | [REDACTED]               |
| [REDACTED]               | [REDACTED]               | [REDACTED]               | [REDACTED]               | [REDACTED]               | [REDACTED]               | [REDACTED]               |
| [REDACTED]               | [REDACTED]               | [REDACTED]               | [REDACTED]               | [REDACTED]               | [REDACTED]               | [REDACTED]               |
| [REDACTED]               | [REDACTED]               | [REDACTED]               | [REDACTED]               | [REDACTED]               | [REDACTED]               | [REDACTED]               |
| [REDACTED]               | [REDACTED]               | [REDACTED]               | [REDACTED]               | [REDACTED]               | [REDACTED]               | [REDACTED]               |
| [REDACTED]               | [REDACTED]               | [REDACTED]               | [REDACTED]               | [REDACTED]               | [REDACTED]               | [REDACTED]               |
| [REDACTED]               | [REDACTED]               | [REDACTED]               | [REDACTED]               | [REDACTED]               | [REDACTED]               | [REDACTED]               |
| [REDACTED]               | [REDACTED]               | [REDACTED]               | [REDACTED]               | [REDACTED]               | [REDACTED]               | [REDACTED]               |
| [REDACTED]               | [REDACTED]               | [REDACTED]               | [REDACTED]               | [REDACTED]               | [REDACTED]               | [REDACTED]               |
| [REDACTED]               | [REDACTED]               | [REDACTED]               | [REDACTED]               | [REDACTED]               | [REDACTED]               | [REDACTED]               |
| [REDACTED]               | [REDACTED]               | [REDACTED]               | [REDACTED]               | [REDACTED]               | [REDACTED]               | [REDACTED]               |
| [REDACTED]               | [REDACTED]               | [REDACTED]               | [REDACTED]               | [REDACTED]               | [REDACTED]               | [REDACTED]               |
| [REDACTED]               | [REDACTED]               | [REDACTED]               | [REDACTED]               | [REDACTED]               | [REDACTED]               | [REDACTED]               |
| [REDACTED]               | [REDACTED]               | [REDACTED]               | [REDACTED]               | [REDACTED]               | [REDACTED]               | [REDACTED]               |
| [REDACTED]               | [REDACTED]               | [REDACTED]               | [REDACTED]               | [REDACTED]               | [REDACTED]               | [REDACTED]               |
| [REDACTED]               | [REDACTED]               | [REDACTED]               | [REDACTED]               | [REDACTED]               | [REDACTED]               | [REDACTED]               |
| [REDACTED]               | [REDACTED]               | [REDACTED]               | [REDACTED]               | [REDACTED]               | [REDACTED]               | [REDACTED]               |
| [REDACTED]               | [REDACTED]               | [REDACTED]               | [REDACTED]               | [REDACTED]               | [REDACTED]               | [REDACTED]               |
| [REDACTED]               | [REDACTED]               | [REDACTED]               | [REDACTED]               | [REDACTED]               | [REDACTED]               | [REDACTED]               |
| [REDACTED]               | [REDACTED]               | [REDACTED]               | [REDACTED]               | [REDACTED]               | [REDACTED]               | [REDACTED]               |
| [REDACTED]               | [REDACTED]               | [REDACTED]               | [REDACTED]               | [REDACTED]               | [REDACTED]               | [REDACTED]               |
| [REDACTED                |                          |                          |                          |                          |                          |                          |

[figure not shown]

## 2 Study objectives and endpoints

### 2.1 Study objectives

#### 2.1.1 Primary objective

- To investigate the safety and tolerability of multiple subcutaneous injections of IBI362 in patients with type 2 diabetes inadequately controlled by lifestyle intervention or metformin, and to determine the safe dose range.

#### 2.1.2 Secondary objectives

- To investigate the pharmacokinetic/ pharmacodynamics (PK/PD) parameters of multiple subcutaneous injections of IBI362 in patients with type 2 diabetes inadequately controlled by lifestyle intervention or metformin.

### 2.2 Study Endpoints

#### 2.2.1 Primary endpoint

- **Safety and tolerability:** During dose escalation, the incidence and severity of adverse events at each dose level, including chief complaint, physical examination, laboratory tests (hematology, blood chemistry, lipid panel, coagulation function, urinalysis, myocardial enzymes, serum amylase and/or lipase, thyroid function, calcitonin, etc.), vital signs (pulse, respiration, blood pressure, body temperature), 12-lead ECG and other examinations; treatment compliance; and record the name, clinical characteristics, severity, start and stop time, supportive care and outcomes of adverse events, correlation with the study drugs;

- **Maximum tolerated dose:** If the dose exploration is stopped when the criteria for stopping dose escalation are met at a certain dose level, the previous dose is the maximum tolerated dose. If the criteria are still not met when the maximum exploratory dose is reached, the maximum tolerated dose is greater than or equal to the maximum escalation dose.

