## 7 STUDY ASSESSMENTS

### 7.1 Safety and Tolerability Assessments Metrics

- **Safety and tolerability:** During dose escalation, the incidence and severity of various adverse events at different dose stages will be recorded. The main complaints of patients, physical examination, laboratory tests (blood routine, blood biochemistry, blood lipid, coagulation function, urine routine, myocardial enzyme spectrum, serum amylase and/or lipase, thyroid function, calcitonin, etc.), vital signs (pulse, respiration, blood pressure, body temperature), 12-lead ECG and other examinations; medication compliance analysis will be performed to determine the correlation with the study drug and record the name, clinical characteristics, severity, occurrence and end time, treatment methods and outcomes of adverse events, correlation with the study drug and other information;
- **Maximum tolerated dose:** If the dose exploration is stopped when the criteria for stopping dose escalation are met at a certain dose level, the previous dose is the maximum tolerated dose. If the criteria are still not met when the maximum exploratory dose is reached, the maximum tolerated dose is greater than or equal to the maximum escalation dose;

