#### **3.4 PHARMACODYNAMIC PARAMETERS**

- To assess the pharmacodynamic parameters of IBI362 after multiple doses: changes in fasting blood glucose, insulin, fasting C-peptide, HbA1c, endogenous OXM and GLP-1 before and after administration;
- Changes in fasting blood glucose and insulin at steady state in each dose phase during dose escalation;
- The change of each parameter of MTT test from baseline after multiple dose administration;

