## **6 Statistical Analysis Methods**

### **6.1 GENERAL PRINCIPLES**

All statistical analyses will be performed using SAS 9.4 (or later version). This trial is mainly based on descriptive statistics, and in principle, no comparison will be made.

All data collected in this study will be presented in data listings and summarized in tables by treatment group, unless otherwise specified. Subjects receiving placebo in different cohorts will be combined and analyzed in summary tables.

Categorical data were presented as frequency (percentage). Unless otherwise specified, the number of subjects in each treatment group in the corresponding study population will be the denominator for the percentages. Percentages will be displayed to 1 decimal place.

Continuous data will be shown as mean  $\pm$  standard deviation or median (minimum, maximum). The mean and median will be displayed to 1 more decimal place than the original data, the standard deviation will be displayed to 2 more decimal places than the original data, and the maximum and minimum values will be displayed to the same decimal place as the original data. For PK parameters, geometric means and coefficients of variation will be displayed to the first decimal place, unless otherwise specified.

Baseline value: defined as the last available measurement prior to receiving the first dose of study treatment.

The following notation will be used in the tables of statistical analysis:

| Treatment Group in Protocol                                   | Treatment Groups in Statistical Analysis |
|----------------------------------------------------------------------|-------------------------------------------------|
| Cohort 1, treated with IBI362                                 | IBI362 – Cohort 1                               |
| Cohort 2, treated with IBI362                                 | IBI362 – Cohort 2                               |
| Cohort 3, treated with IBI362                                 | IBI362 – Cohort 3                               |
| Cohort 1, Cohort 2, Cohort 3, Placebo Treated                 | Placebo                                         |
| Cohort 1, Cohort 2, Cohort 3, treated with dulaglutide 1.5 mg | Dulaglutide 1.5 mg                              |

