### **6.6.1 Adverse events**

Classified by date of event:

- Pre-treatment Adverse Events: Adverse events that occurred from signing of informed consent until the first dose of study treatment.
- Treatment-emergent adverse events (TEAEs): Adverse events that occurred or became serious during the first dose of study treatment through 56 days after last dose.
- Post-treatment adverse events: Adverse events that occurred or became serious after 56 days following the last dose until the end of the trial.

If the AE start date is completely/partially missing, impute the date according to Section 5.3 before assigning pre-treatment/on-treatment/post-treatment adverse events.

The incidence (frequency) of all AEs, TEAEs, severe TEAEs, TEAEs leading to permanent treatment discontinuation, drug-related TEAEs (TRAEs), severe TRAEs, TRAEs leading to permanent treatment discontinuation, AESIs, severe AESIs, AESIs leading to permanent treatment discontinuation, SAEs, SAEs related to study drug, and SAEs leading to permanent treatment discontinuation will be summarized by treatment group.

The following categories of adverse events will be summarized by SOC, PT, and SOC, PT, and severity from MedDRA coding:

- TEAEs
- TEAE leading to permanent discontinuation
- TRAE
- TRAEs leading to permanent discontinuation
- AESI
- AESIs leading to permanent discontinuation
- For gastrointestinal reactions, the number of events with gastrointestinal reactions was also provided. Gastrointestinal reactions including adverse reactions with preferred terms of nausea, vomiting, diarrhea, dyspepsia, abdominal distension, abdominal discomfort, and gastroesophageal distress

TEAEs will also be summarized by PT in MedDRA and the number of events of TEAEs will be calculated.

Treatment-emergent SAEs, treatment-emergent SAEs related to study drug, and treatment-emergent SAEs leading to permanent discontinuation will be summarized by SOC and PT.

Hypoglycemic events will be summarized by treatment group.

The above summary tables are sorted according to the incidence of AEs in all subjects who received IBI362.

Subjects who discontinued treatment due to AEs, subjects who experienced SAEs, and subjects who died will be listed (at least include AE start date, end date, severity, relationship with drug, action taken, and outcome). All AEs will be listed.

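### The primary endpoint asks for adverse event incidence at each dose level, but the planned tables count events only by cohort, and each IBI362 cohort takes three doses

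*Combined protocol and SAP*

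**What the plan says.** Protocol section 2.2.1 gives the primary safety endpoint as "During dose escalation, the incidence and severity of adverse events at each dose level". SAP section 3.1 repeats it. Protocol section 7.1 words the same idea as "the incidence and severity of various adverse events at different dose stages will be recorded".

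Under the Synopsis dosing regimen, each IBI362 cohort takes three doses for 4 weeks each: 1.0, 2.0 and 3.0 mg in Cohort 1; 1.5, 3.0 and 4.5 mg in Cohort 2; 2.0, 4.0 and 6.0 mg in Cohort 3.

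For the tables, SAP section 6.1 says that data are "summarized in tables by treatment group, unless otherwise specified". Its list of groups defines the IBI362 groups by cohort, for example "Cohort 3, treated with IBI362". SAP section 6.6.1 applies this to adverse events: the overview runs through to "SAEs related to study drug, and SAEs leading to permanent treatment discontinuation will be summarized by treatment group", and the further tables are by system organ class, preferred term and severity. Protocol section 9.4.3 likewise summarises by arm. A single window defines a treatment-emergent event: "Adverse events that occurred or became serious during the first dose of study treatment through 56 days after last dose". SAP section 6.6.1 also states "All AEs will be listed", and section 6.4.1 provides a listing of exposure.

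**The concern.** The endpoint is defined per dose, and the table is built per titration regimen. The primary objective (protocol section 2.1.1) is to find the safe dose range. A cohort column cannot show whether events began at the starting dose, after a step up, at the final dose or after treatment ended.

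The published supplement shows the effect. Table S3 heads the three IBI362 columns 3.0, 4.5 and 6.0 mg. Decreased appetite appears in 4 of 8 patients under 4.5 mg, but the table cannot say whether it began at 1.5, 3.0 or 4.5 mg or in follow-up. That distinction bears on the choice of starting dose and titration step.

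**Working it through.** **The plan's own figure.** Three cohorts randomised 8:4:2 give 3 × (8 + 4 + 2) = 42, as stated in protocol section 9.2. Of these, 3 × 8 = 24 are planned to receive IBI362. No power calculation is given, so none can be checked.

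**What dose level means.** Three places point to the dose being taken:
- Protocol section 7.1 speaks of dose stages (quoted above).
- Protocol section 2.2.2 has a secondary endpoint on steady-state glucose, insulin and glucagon at each dose level during escalation. SAP section 3.4 restates it as "Changes in fasting blood glucose and insulin at steady state in each dose phase during dose escalation". A cohort is not a phase of escalation; a 4-week step is.
- Two stopping criteria in protocol section 3.2.3 count patients at a single dose: at least 4 with related symptomatic hypoglycaemia, and at least 2 with severe related non-serious events.

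**Counting.** Three cohorts × three steps = 9 cohort-steps. The distinct planned doses are 1.0, 1.5, 2.0, 3.0, 4.0, 4.5 and 6.0 mg, which makes 7; the backup doses of 2.25 and 3.75 mg would make 9. The planned tables have 3 IBI362 columns. The 2.0 mg dose occurs in Cohorts 1 and 3, and 3.0 mg in Cohorts 1 and 2, each for up to 8 + 8 = 16 patients split across two columns.

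**What one column pools.** The Schedule of Activities puts doses on Days 1, 8, …, 78. The window closes 56 days after the last dose: 78 + 56 = Day 134. For a Cohort 3 patient who completes on schedule:

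| Period | Days | Length | Share of 134 |
|---|---|---|---|
| 2.0 mg | 1–28 | 28 | 20.9% |
| 4.0 mg | 29–56 | 28 | 20.9% |
| 6.0 mg | 57–84 | 28 | 20.9% |
| Follow-up | 85–134 | 50 | 37.3% |

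Time below the final dose is 56/134 = 41.8% of the window and 56/84 = 66.7% of the treatment days. Cohorts 1 and 2 divide in the same way. These are shares of calendar time, not of events.

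**Can the stopping rules still be checked from cohort columns?** Sometimes. Table S3 shows hypoglycaemia in 1, 0 and 1 patients, 2 in total, so no dose can have reached 4. The rule of 2 severe related events is harder to check: two such patients in one column may or may not have been on the same dose, and if the rule is counted across cohorts, one patient in Cohort 1 and one in Cohort 2 could both have been on 3.0 mg.

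**The case against.** The strongest reply is that dose level means cohort. There is support for this. Protocol section 5.1.2 and SAP section 2.4 describe randomisation 8:4:2 at each dose, where dose can only mean cohort. Protocol section 9.2 refers to dose cohorts, sections 9.4.1 and 9.4.2 use dose group for an IBI362 arm, and section 3.1.1 describes the trial as studying three regimens. On that reading the cohort tables are the endpoint. The ambiguity is real and should be acknowledged, but the dose-stage wording, the steady-state endpoint and the same-dose stopping counts make the step the more natural reading.

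Other parts of the reply stand:
- The endpoint sentence also covers vital signs and ECG. SAP sections 6.6.3 and 6.6.4 summarise these by visit or evaluation time, so they can be lined up with dose steps. The point is confined to the adverse event tables.
- Events and exposure are listed, so dose at onset can be recovered for 24 planned patients. SAP section 5.3 even has date rules for marking the cycle number of an event. No table is attached to either.
- SAP section 2.5.2 records no change to this endpoint, and a reader might infer that the SAP quietly departed from the protocol. It did not: protocol section 9.4.3 already summarised by arm. The mismatch lies between the protocol's endpoint and its own analysis section, and the SAP carries it forward.

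A reader might also infer that the maximum tolerated dose is wrong or cannot be verified. The documents do not support that. Escalation is decided during the trial by the investigator and the sponsor (protocol section 3.2.3), the sponsor is unblinded (section 5.1.2), and low cohort counts bound the per-dose counts, as shown above.

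**Conclusion.** The point holds as a reporting gap in the adverse event part of the primary endpoint. Following the plan exactly gives incidence over a titration regimen plus follow-up, with 28 of 134 days (20.9%) at the cohort's final dose, and no planned table gives incidence at a dose. This rests on reading dose level as the dose being taken, which the documents favour without settling, and on a patient who completes on schedule. It is worth correcting because it concerns the primary endpoint and the correction is cheap. It does not undermine the cohort tables, the stopping criteria or the maximum tolerated dose definition.

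**What to change.** In SAP section 6.6.1, add one descriptive table of treatment-emergent events (overall, by severity, and for the event types in protocol section 3.2.3) by cohort and dose step at onset:
- **Rows or columns:** 1.0/2.0/3.0 mg for Cohort 1; 1.5/3.0/4.5 mg for Cohort 2, plus 2.25 or 3.75 mg if a backup schedule is used; 2.0/4.0/6.0 mg for Cohort 3. Keeping 2.0 and 3.0 mg separate by cohort is a judgement, made because titration history differs.
- **Denominator:** patients who received at least one dose at that step.
- **Assignment:** the most recent step started, up to the first dose of the next step. A fixed 7-day limit between steps would not work, because the ±2 day visit windows allow up to 11 days between the Day 22 and Day 29 doses (Day 20 to Day 31).
- **Off treatment:** events in a backup break week, or after a pre-stated cut-off following the last dose of treatment, go in a separate column. Without a cut-off the last step would run from Day 57 to Day 134, or 78 days. The sponsor should choose it from what is known of the drug's persistence, since the documents give no half-life value.
- **Incomplete onset dates:** show as step unknown if the event cannot be placed. SAP section 5.3 would move a fully missing start date to the first dose and so inflate the starting step.

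Keep the cohort tables, stopping criteria and maximum tolerated dose definition. If the sponsor did intend dose level to mean cohort, SAP section 3.1 should say so.

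The cost is one table from dates already collected, with no new patients, visits or protocol change. The downside is cells of 8 or fewer and dose confounded with time on treatment, so the table must be labelled descriptive and not used to compare doses.
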